# Methods

### Setting:

The study will be conducted at Mulago Hospital, a national referral and teaching hospital. The department of Obstetrics and Gynaecology is currently housed at Kawempe Hospital. The Maternal Fetal Unit (MFM) of the department admits approximately 2100 pregnant women per month. Among the MFM admissions, 7% of them are preeclamptic/eclamptic women. The women with preeclampsia and eclampsia are managed in two wards by carders of health workers ranging from senior consultants to intern doctors. The midwives are the ones who administer the medication.

### Trial design:

Randomized Open label Clinical Trial

### Study participants:

Inclusion criteria:

1. The study will include pregnant women 20+ weeks of gestation or delivered within 24 hours,
2. Presenting with preeclampsia and eclampsia i.e. have a raised blood pressure (systolic of >140 mmHg and diastolic > 90mmHg), proteinuria >1+.
3. Present within the study period
4. Consent to participate in the study.

Exclusion criteria:

1. Pregnant women or delivered within 24 hours who admitted with had received magnesium sulphate 24 hours prior to admission,
2. Has known allergy to magnesium sulphate and
3. Has elevated serum creatinine (>1.2 mg/dl). However the participants may be enrolled prior to the knowledge of serum creatinine, but withdrawn if the level is >1.2 mg/dl.

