# Abstract

**Introduction:** Magnesium Sulphate is the drug of choice for prevention and treatment of seizures in preeclampsia and eclampsia. It is administered parenterally by intravenous (IV) and or intramuscular (IM) routes. The IM regimen used in low resource settings, requires repeated painful injections which may be a barrier to optimal utilization whereby, there is frequent omission of some doses or increased interval between maintenance doses and low patient acceptability of magnesium. In addition, the IM regimen may potentially lead to abscess formation. There is a need to test an alternative way of providing Magnesium Sulphate that avoids the adverse events of IM regimens.

**Objective:** To assess the acceptability and safety of Springfusor device in the administration of magnesium sulphate in preeclampsia and eclampsia.

**Methods:** The study will be open label clinical randomized trail conducted at Mulago national referral and teaching hospital, where, 482 women diagnosed with preeclampsia and eclampsia will be randomized in blocks to either Springfusor device or standard of care for the administration of magnesium sulphate. Women in the Springfusor group will have their loading dose (4 gm of 50% Magnesium sulphate in 10 ml syringe administered over 20 minutes) and maintenance therapy (4 gm of 50% Magnesium sulphate in 10 ml syringe administered over 4 hours. The 4 gm maintenance dose will be repeated every 4 hours for 24 hours) of Magnesium sulphate through an IV infusion administered using a Springfusor pump. The control group will have Magnesium sulphate administered according to the Pritchard regimen (standard hospital practice). The Pritchard regimen involves administration of loading dose of 4 gm of 20% Magnesium sulphate IV over 15-20 minutes, immediately followed by 10 gm of 50% Magnesium sulphate IM (5gm on each buttock). The maintenance dose of 5 gm of 50% Magnesium sulphate IM every 4 hourly in alternate buttocks continued for 24 hours.

The primary outcome is the acceptability of administration of Magnesium sulphate using Springfusor assessed using a Likert scale. The other outcomes are discontinuation and complications in the two arms. Analysis will be intention to treat.

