# Introduction

Preeclampsia is a disorder that presents with a raised blood pressure and proteinuria in pregnancy through to postnatal period [[1](#_ENREF_1)]. Globally, preeclampsia complicates approximately 2-8% of the pregnancies [[2](#_ENREF_2)] The presence of convulsions with preeclampsia indicates eclampsia, however, occasionally seizures may occur in the absence of hypertension and/or proteinuria . Preeclampsia and eclampsia (PE/E) are life-threatening for both the mother and the fetus. Preeclampsia and eclampsia are among the leading causes of maternal deaths and disability worldwide, more especially in the low resource setting [[2](#_ENREF_2)]. The World Health Organization (WHO) estimates that, 16% of the maternal deaths in low resource settings are due to PE/E [[3](#_ENREF_3)]. According to 2016 annual report of Mulago National teaching hospital, PE/E ranked second to hemorrhage as a specific, direct cause of maternal deaths, accounting for 21% of the maternal deaths (.

Magnesium Sulphate is the drug of choice for prevention and treatment of Eclampsia [[3](#_ENREF_3)]. It is administered parenterally by intravenous (IV) and or intramuscular (IM) routes. The IV regimen achieves more stable serum levels of Magnesium Sulphate but requires the use of electronic infusion pump for safe delivery. In low resource settings, electric infusion pumps are not available or feasible. The IM regimen used in low resource settings, requires repeated painful injections which may be a barrier to optimal utilization whereby, there is frequent omission of some doses or increased interval between maintenance doses and low acceptability of magnesium sulphate. In addition, the IM regimen may potentially lead to abscess formation. There is a need to develop an alternative way of providing Magnesium Sulphate that avoids the adverse events of IM regimens that can be used in low resource settings.

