## Diagnosis of preeclampsia

Preeclampsia is a multisystem disease characterized by hypertension accompanied by proteinuria. The new onset of hypertension after 20 weeks of pregnancy (a systolic BP of >140 mmHg or a diastolic blood pressure >90 mmHg), with the new occurrence of proteinuria (>0.3g/24 hours) is the criteria for diagnosis of preeclampsia [[1](#_ENREF_1)]. Preeclampsia is usually classified as non-severe or severe [[3](#_ENREF_3)]. Progression to severe can be fast, unanticipated and fulminant. Preeclampsia is not considered severe until systolic or diastolic blood pressure exceed 160 mmHg or 110 mmHg respectively [[6](#_ENREF_6)]. The American College of Obstetricians and Gynaecologists recommend that the diagnosis of hypertension requires at least two measurements of blood pressure taken 4 hours apart, however when the blood pressures are severe, the diagnosis can be confirmed within minutes to enable timely antihypertensive therapy [[1](#_ENREF_1)]. It is also recommended that the diagnosis of proteinuria is when a 24 hour excretion equals or exceeds 300 mg/l. However, when a quick decision is require or the facility is not able to perform 24 hour protein estimation, a urine dipstick reading of 1+ is suggestive of proteinuria [[1](#_ENREF_1)].

Women with mild preeclampsia usually are asymptomatic. However those with severe preeclampsia may have headache, blurring of vision and abdominal pain (epigastric). Maternal organ dysfunction associated with severe preeclampsia may present with HELLP syndrome (hemolysis, elevated liver enzymes and low platelets), eclampsia, stroke and disseminated intravascular coagulation [[2](#_ENREF_2), [3](#_ENREF_3)]. Leeman and colleagues have indicated that the presence of the following are features of severe preeclampsia; elevated creatinine level (>1.1mg/dl), hepatic dysfunction (transaminase levels > 2 times upper limit of normal or right upper quadrant or epigastric pain, new onset of headache or visual disturbance, pulmonary oedema and or platelet count < 100x10^9^ per l [[6](#_ENREF_6)]

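### Inclusion criterion 2 joins the blood pressure cut-offs with *and*, while the protocol's own diagnostic criteria for preeclampsia join the same cut-offs with *or*

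*Protocol*

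**What the plan says.** Criterion 2 of the inclusion criteria (Protocol, Study participants) admits women presenting with preeclampsia and eclampsia, and then spells out with *i.e.* what that means: they "have a raised blood pressure (systolic of >140 mmHg and diastolic > 90mmHg), proteinuria >1", followed by a plus sign, so a dipstick reading above 1+.

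The section Diagnosis of preeclampsia (Protocol, Literature review) states the blood pressure part of the diagnosis as "a systolic BP of >140 mmHg or a diastolic blood pressure >90 mmHg" and completes it "with the new occurrence of proteinuria (>0.3g/24 hours) is the criteria for diagnosis of preeclampsia". Where a quick decision is needed or 24-hour estimation is not available, it adds that "a urine dipstick reading of 1+ is suggestive of proteinuria". Its severity rule also joins the two pressures with *or*: "Preeclampsia is not considered severe until systolic or diastolic blood pressure exceed 160 mmHg or 110 mmHg respectively".

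The Abstract describes the trial population by diagnosis, without narrowing it: "482 women diagnosed with preeclampsia and eclampsia will be randomized in blocks". The Operational definition list does not define preeclampsia. No other section widens criterion 2 or explains a restriction.

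**The concern.** The numerical cut-offs in the two sections are identical and only the connective differs. Because criterion 2 is introduced with *i.e.*, it reads as the meaning of the condition and not as a chosen subgroup. A reader therefore has two incompatible statements of who has the condition under study, and the stricter one is the operative entry rule.

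The hypothesis, the objectives and the argument for scale-up all concern women with preeclampsia and eclampsia in general. If screening follows criterion 2 to the letter, the trial enrols a narrower group than the one its conclusion names. If screening follows the diagnostic criteria, some enrolled women fail a written inclusion criterion and could be counted as eligibility deviations. Entry criteria belong to the protocol, so a statistical analysis plan cannot settle this.

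**Working it through.** No figure of the plan is in dispute, so the check is a comparison of texts.

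**1. Blood pressure.** Take a woman who otherwise qualifies, with new-onset hypertension after 20 weeks and 2+ protein. Two yes/no conditions give four cells:

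| Systolic >140 | Diastolic >90 | Diagnosis of preeclampsia (*or*) | Criterion 2 (*and*) |
|---|---|---|---|
| yes | yes | meets | meets |
| yes | no, e.g. 150/88 | meets | **fails** |
| no | yes, e.g. 138/96 | meets | **fails** |
| no | no | fails | fails |

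The two rules agree in the first and last cells and conflict in the middle two. The severity rule sharpens the conflict: a systolic above 160 mmHg with a diastolic of 90 or below passes the protocol's systolic cut-off for severe disease, yet fails criterion 2 read literally.

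**2. Proteinuria.** Criterion 2 asks for "proteinuria >1" with a plus sign after it. Read strictly, that means 2+ or more, so a reading of exactly 1+ fails. The Diagnosis section says "a urine dipstick reading of 1+ is suggestive of proteinuria". These conflict only if the sign is meant strictly. The Diagnosis section gives its 24-hour threshold once as above 0.3 g and once as equal to or above 300 mg, so the document does not use the sign consistently. This part remains open.

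**3. Effect on the sample size.** The inputs in the Sample size section are control acceptability 31%, a relative increase of 50%, power 90% and alpha 0.05 (two-sided assumed, since the section does not say).

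- p1 = 0.31; p2 = 0.31 × 1.5 = 0.465; d = 0.155; mean p = 0.3875.
- Uncorrected: n = [1.960 × √(2 × 0.3875 × 0.6125) + 1.282 × √(0.31 × 0.69 + 0.465 × 0.535)]² / 0.155², which rounds up to 206.
- With continuity correction: n′ = (n/4) × [1 + √(1 + 4/(n × d))]², which rounds up to 219, the stated figure.
- 219 × 1.10 = 241 per arm, also as stated, and 2 × 241 = 482.

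No eligibility threshold enters this calculation, so the choice between *and* and *or* leaves it unchanged.

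**4. Effect on the comparison.** The Randomisation section allocates women only after they have qualified and consented, from sealed opaque envelopes. Whichever rule is used, it acts before allocation and equally on both arms.

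**5. Number of women affected.** The Setting section gives 2100 admissions a month, 7% with preeclampsia or eclampsia: 0.07 × 2100 = 147. The share of these in the two conflicting cells is not given and cannot be derived from anything in the document.

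**The case against.** The strongest reply is that this protocol often writes *and* where only *or* makes sense. Criterion 2 itself speaks of preeclampsia *and* eclampsia without meaning both at once. The exclusion list joins allergy and raised creatinine with *and*, although either plainly excludes. The primary outcome counts ratings of 1 *and* 2 as acceptable, though no woman gives both. On that usage the bracket may simply list two thresholds. The reply adds that the Diagnosis section is literature review, that entry criteria may be narrower than a textbook diagnosis, and that the team will be trained and have a procedure manual.

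Much of this stands. It makes a drafting slip more likely than an intended restriction, and it means one cannot assert that these women will in fact be turned away. It does not remove the conflict. An eligibility line is applied as a checklist, the *i.e.* presents it as the definition, and no restriction is declared. Training and a manual help only if the text they convey is settled.

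A reader might infer more in four ways, none of which the documents support:

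- **That women with 1+ protein are certainly excluded against the protocol's own definition.** The Diagnosis section calls 1+ only suggestive, limits it to quick decisions or lack of 24-hour testing, and uses the greater-than sign loosely.
- **That criterion 2 contradicts the protocol on eclampsia.** The Introduction does say that "occasionally seizures may occur in the absence of hypertension and/or proteinuria", but as an occasional exception; its main description is convulsions together with preeclampsia. Not providing for a rare presentation is not a contradiction.
- **That a monthly number of lost women can be quoted.** Any share applied to the 147 admissions would be invented. The 147 is also counted before the exclusions and consent.
- **That staff will screen unevenly.** This is possible with two definitions in one document, but nothing shows that it will happen.

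**Conclusion.** Wrong as written, minor. Criterion 2 and the Diagnosis section give the same blood pressure cut-offs with opposite connectives. Applied literally, the entry rule excludes women with only one pressure raised who have the condition named in the objectives. This rests on reading *and* in its ordinary sense and on the absence of any stated restriction. The proteinuria threshold is a secondary ambiguity and disappears if the sign means 1+ or more.

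The effect is confined to the definition of the enrolled population, consistent screening and generalisability, and its size cannot be computed from the documents. A reader might suspect bias between the arms or a wrong sample size. Neither follows: eligibility is fixed before concealed allocation, and the 219 per arm does not depend on it. Nor do the documents show that acceptability differs between women with one and with both pressures raised, so a distorted result is not established.

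**What to change.** Reconcile the inclusion criteria with the section Diagnosis of preeclampsia, so that one definition holds throughout. Either:

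- write criterion 2 and the screening form with the connective that the Diagnosis section uses; or
- if the narrower group is intended, say so in criterion 2, give the reason, and limit the conclusion to women with both pressures raised.

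In the same edit, state whether the dipstick threshold includes a reading of exactly 1+.

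The cost is one line of the eligibility criteria, the matching line of the screening form, and ethics committee approval of the amendment, which the protocol requires for any modification. The sample size, randomisation and analysis do not change. Under the first option recruitment can only stay the same or improve.

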### Intervention

Women in the intervention arm (Springfusor group) will have their loading and maintenance therapy of magnesium sulphate using IV infusion administered using a Springfusor infusion pump. The loading dose will be 4 gm of 50% magnesium sulphate in 10 ml syringe administered over 20 mins. The maintenance dose of 4 gm of 50% magnesium sulphate in 10 ml will administered over 4 hours. The 4 gm dose will be repeated every 4 hours for 24 hours

Women in the control arm (Standard of care group) will have magnesium sulphate administered according to the standard hospital practice. The loading dose of is administered using an IV-push in which health worker manually and slowly inject 4 gm of 20% Magnesium sulphate in 20 ml syringe over 15-20 minutes. This is immediately followed by IM injection of 10 gm of 50% magnesium sulphate and 1 ml of lignocaine into the gluteal muscles (5 gm on each buttocks). The maintenance dose of 5 gm IM injection every 4 hourly for 24 hours. Over the 24 hour period the intravenous group (intervention) would have got 28 gm of magnesium sulphate while the intramuscular group (control) would have received 39 gms. The higher total dose in the control group is assuming a reduce bioavailability of intramuscular drug.

### Sample size

In the Mundle et al trial[[16](#_ENREF_16)], the Pritchard regimen (IM maintenance) the acceptability of magnesium sulphate was 31%. We are assuming that the women in Springfusor are likely to find magnesium sulphate administration more acceptable by 50%. With power of 90 and alpha of 0.05, we estimate that we need 219 women with preeclampsia in each arm. With approximately 10% non-response, we need 241 women in each arm.

### Randomisation

A biostatistician at the Clinical Epidemiology Unit of Makerere University College of Health Sciences and not involved in the clinical trial will develop allocation sequence using an online computer random number generator in different block sizes. Women with preeclampsia and eclampsia will be randomized to have their magnesium sulphate administered with Springfusor pump or the hospital standard of care. The study participants will be randomized only after they have qualified for the study and signed informed consent. Serially numbered sealed opaque envelopes (concealed allocation) containing the randomization group will be provided at site in a secure place within the ward. Trained research staff will open the envelope to determine the group assignment after the participant is enrolled, completed all the baseline assessment and it is time to allocate the intervention

Blinding: Because of the nature of the study, it is difficult to blind the study, the implementation of the allocation and measurement of the outcome.

### Trial flow chart

| [figure not shown]  **Elevated creatinine level (>1.2 mg/dl)**  **eclampsia** |
| --- |

### Study procedure

Women with preeclampsia and eclampsia admitted at Mulago hospital maternal fetal unit will be screened and enrolled into the study if they meet the inclusion criteria. Both arms will receive the standard care as is currently given to women with preeclampsia in the health facilities; which includes management of high blood pressure, laboratory investigations (urine analysis, RFTs & LFTs) and delivery as planned by the attending physicians. Upon enrolment, study participants will receive the magnesium sulphate as per the randomization and any medication prescribed by the attending physician and received by the woman will be recorded in the CRF. The time it takes to administer the loading dose will be measured. Similarly the time it takes to administer the maintenance dose using the Springfusor will be measured using stop clock from the loading of the magnesium sulphate into device to completion of the medicine in the syringe.

The study participant’s respiratory rate will be monitored by the study midwives every 5 minutes during the loading dose (30 minutes). During the 24 hours maintenance dose, the participant’s respiratory rate, urine output and tendon reflexes will be monitored hourly. In addition, at four hourly interval, other side effects of magnesium sulphate like nausea, vomiting, flushing of the skin, muscle weakness, confusion and drowsiness will be noted. A report of pain and sign of inflammation will also be noted. The study participants will be followed till discharge and the women’s outcomes of the pregnancy will be reported. All women enrolled in the study will have an interview performed before discharge from the hospital. Study staff will administer a brief interview to capture information on the woman’s acceptability of magnesium sulphate using Likert scale, including the degree of pain experienced during administration of magnesium sulphate using a visual analogue scale. A standard operating procedure manual will be produced and provided to the study staff to enable adherence to the protocol.

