- *Feasibility of Springfusor pump use: ⃰* The proportion of women who have a Springfusor used for administration of magnesium sulphate and experience some technical problem with its use, blockage of FCT, the number of attempts made prior to successful Springfusor placement, the number of failed Springfusor placement and the number of FCTs and spilled magnesium sulphate used will also be documented.
- The *reliability** of the Springfusor to administer magnesium sulphate in the prescribed time will assessed for the loading period and the maintenance period. The intra-correlation coefficient for the device will be calculated.

These outcomes will be compared between the women in the two arms. A *outcome will be reported only for women who will have magnesium sulphate administered using Springfusor

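### The Springfusor timing starts when the device is loaded, not when flow to the patient begins, so set-up counts as infusion time; how the end is observed is left open

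*Protocol*

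**What the plan says.** All references are to the protocol.

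- **Outcome.** Outcome Measures says the reliability "of the Springfusor to administer magnesium sulphate in the prescribed time will assessed for the loading period and the maintenance period", and that an intra-class correlation coefficient (ICC) will be calculated. Data analysis labels an ICC below 0.4 as poor and 0.4 to 0.75 as fair. Reliability under repeated use is the fourth secondary objective.
- **Prescribed times.** Under Intervention: "The loading dose will be 4 gm of 50% magnesium sulphate in 10 ml syringe administered over 20 mins"; and "The maintenance dose of 4 gm of 50% magnesium sulphate in 10 ml will administered over 4 hours".
- **Loading-dose clock.** Study procedure says "The time it takes to administer the loading dose will be measured", with no start or end point.
- **Maintenance clock.** The next sentence, joined by the word Similarly, times the maintenance dose "using stop clock from the loading of the magnesium sulphate into device to completion of the medicine in the syringe".
- **Scheduled attendance.** In maintenance, "the participant’s respiratory rate, urine output and tendon reflexes will be monitored hourly". During loading, respiratory rate is checked every 5 minutes. Neither schedule mentions the clock or the syringe.
- **Set-up difficulty.** The feasibility outcome counts attempts before successful placement, failed placements, blocked flow control tubes and spilled drug.

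**The concern.** The outcome compares delivery time with a target, so the measured interval should run from the start of flow into the patient to the end of flow. The stated interval starts earlier, at loading of the device. Connection, repeated attempts and tube replacement can all fall between the two, and the protocol foresees such difficulties. Time lost there is added to the recorded infusion time. The error has one direction: it lengthens recorded times, so a pump that runs somewhat fast can look on target and a correct one can look slow. If set-up time varies between uses, it also adds variation that does not come from the pump, which lowers the ICC.

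The end of the interval is a defined event, but the protocol does not say who observes it or how. That matters more in maintenance, where scheduled contact within a dose is hourly, than in loading, where staff attend every 5 minutes.

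**Working it through.** The protocol gives no numerical result or precision target for reliability, so there is no plan figure to reproduce. The trial's sample size plays no part here.

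**Inputs from the protocol:** targets of 20 and 240 minutes; clock start at loading of the device; hourly clinical checks in maintenance; ICC cut-off 0.4. **Assumptions:** set-up time, the way emptying is noticed, and the spread of infusion times between and within devices.

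**Model.** Recorded time R = S + T + D, where S is time from loading the device to flow, T is true infusion time, and D is delay until the empty syringe is noticed. Only T is wanted.

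**1. Effect of the start point, with D = 0.** Relative excess = S / target.

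| Assumed S | Maintenance, S/240 | Loading, S/20 (only if the same start applies) |
|---|---|---|
| 2 min | 0.8% | 10% |
| 5 min | 2.1% | 25% |

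A pump reads exactly on target when T = target − S. With S = 5 in maintenance, T = 235, a pump 2.1% fast (240/235 = 1.021). With S = 5 in loading, T = 15, a pump 33% fast (20/15 = 1.33); with S = 2, T = 18, 11% fast (20/18 = 1.11).

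**2. Effect of variable set-up on the ICC.** ICC = between-device variance / (between + within + error variance). If S varies uniformly from 2 to 5 minutes, independently of the device, its variance is 3²/12 = 0.75.

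- Maintenance, assumed SDs 10 (between) and 5 (within) minutes: 100/125 = 0.80 becomes 100/125.75 = 0.80. No visible change. If S ranged from 0 to 10 minutes (variance 100/12 = 8.33): 100/133.33 = 0.75.
- Loading, if the same start applies and the same SDs are scaled by 20/240 (0.833 and 0.417 minutes): 0.694/0.868 = 0.80 becomes 0.694/1.618 = 0.43. Scaling SDs of 15 and 5 instead (1.25 and 0.417 minutes): 1.563/1.736 = 0.90 becomes 1.563/2.486 = 0.63.

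**3. Effect of the end point, only if emptying is noticed at hourly checks.** The protocol does not say that it is.

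- Checks aligned with the clock start: R is S + T rounded up to the next 60 minutes. With S = 0, any T above 180 and up to 240 reads 240; T = 185 is 30% fast (240/185 = 1.297). With S = 5, a correct T = 240 becomes 245 and reads 300.
- Checks at random phase: D is uniform from 0 to 60 minutes. T = 185 reads 215 on average and falls within 5% of 240 (228 to 252) with chance (245 − 228)/60 = 28%. T = 200 reads 230 on average, with chance 24/60 = 40%.
- D then has variance 60²/12 = 300 (SD 17.3). The maintenance ICC falls from 0.90 to 225/550 = 0.41 with SDs 15 and 5, and from 0.80 to 100/425 = 0.24 with SDs 10 and 5, below the cut-off of 0.4.

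**The case against.** Five points can be made against this.

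- **The gap may be short.** The section on the Springfusor says that loading the syringe and tube compresses the spring, so flow may follow quickly. This stands for an uneventful set-up. It does not cover repeated attempts, and flow before connection is not delivery to the patient.
- **The start point is stated only for maintenance**, where 2 to 5 minutes is about 1% to 2%. This stands. The larger percentages depend on carrying the rule over to the loading dose through the word Similarly.
- **A constant offset does not change the ICC.** True, but it does shift the comparison with the prescribed time, which is how the outcome is defined, and set-up need not be constant.
- **The promised procedure manual and the five-participant pilot may settle the details.** They may settle how the end is observed. A manual that follows the protocol would keep its start point.
- **Participant safety does not rest on this clock.** This stands: signs of toxicity are monitored directly.

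A reader might also infer that staff attending hourly stop the clock, so that a pump emptying at 185 minutes is recorded as perfect and maintenance times are overstated by 30 minutes (12.5% of 240) on average. The documents do not support this. The clock ends at completion of the syringe, nobody is named to stop it, and the hourly schedule covers clinical signs only. The 185-minute example also needs checks aligned with the clock start, and the 30-minute average needs emptying times spread evenly over the hour between checks.

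**Conclusion.** The point holds for the start of the clock. The stated rule counts time before flow as infusion time and biases recorded times upward. On assumed set-up of 2 to 5 minutes the bias is small in maintenance (0.8% to 2.1%) and material in loading (10% to 25%) only if the same start is used there. The added noise in the ICC follows the same pattern: negligible in maintenance for that range, possibly large in loading.

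For the end of the clock, the finding is that the protocol does not fix how completion is observed. Errors in either direction, a fast pump reading as on time or a correct one reading as slow, follow only if emptying is noted at the hourly checks.

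It would go too far to conclude that the trial cannot answer its repeated-use reliability objective. If set-up is brief and emptying is watched for, the maintenance data remain usable. This is a measurement weakness in a secondary outcome reported for the Springfusor arm only, worth correcting because it is easily avoided.

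**What to change.** In Study procedure, and in the manual and case record form:

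1. Start the clock, for both loading and maintenance doses, when flow to the patient begins, and say explicitly that the same rule applies to both.
2. Record the time from loading the device to flow, and the number of failed attempts, as separate feasibility items.
3. Record how and when the empty syringe was observed: watched to completion, or found empty at a stated time, with the time it was last seen running.
4. Read the remaining syringe volume at the hourly checks already scheduled, as a supporting measure of delivery rate.

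No visits or equipment are added, and no dose or clinical rule changes. The cost is a few extra fields on the form, brief training and some reading error on the syringe scale. The five-participant pilot can test whether the scale is legible in the loaded device, which the protocol does not say.
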